## Potential pitfalls and counteracting measures

This protocol was designed with the main purpose of answering the question “Does tDCS combined with PES have an additive effect in the control of osteonecrosis joint pain associated with SCD?” As in any clinical trial, risk of bias and errors exist. Several strategies will be used to reduce them:

### Potential errors

The development of this protocol involved several experts to carefully design the interventions in order to reduce systematic errors. To minimize human errors, all personnel involved in data collection will be thoroughly trained on how to use study questionnaires and instruments.

### Potential sampling biases

According to the Ficat classification (Ficat, 1985), the femoral head osteonecrosis has four radiographic stages of progressive severity. However, the study sample will not be stratified by degree of femoral osteonecrosis because the association between radiographic examinations and pain intensity is weak (Bedson and Croft, 2008). The randomization method used will likely reduce sampling biases by distributing patients at different osteonecrosis stages equally among groups (Kang et al., 2008). Including only hip joint osteonecrosis may limit the generalization to the larger population of individuals with SCD. Nonetheless, this chronic musculoskeletal pain condition has high prevalence among individuals with SCD (Milner et al., 1991; Hernigou et al., 2006).

### Potential intervention biases

Stimulation duration in this study will differ between neuromodulatory techniques, being 20 min for tDCS and 30 min for PES. The choice for a longer time of PES stimulation was based on studies demonstrating that 30 min provides significant improvement on cortical excitability (McKay et al., 2002). To avoid proficiency bias, interventions will last 30 min. Studies using neuromodulatory techniques, such as tDCS and sensory PES, have shown that one of the reliable alternatives for performing blinding is to instruct participants that they may or may not feel the stimulation (McDonnell et al., 2007; Schabrun et al., 2013, 2014). A recent study using tDCS for 30 min showed that the erythema in the supra-orbital region can occur, ranging from mild to moderate, and may interfere with the study blinding (Ezquerro et al., 2017). To avoid that, participants in this study will not be able to look at their faces during the stimulation procedure. Thus, they will not be able to recognize any erythema over their frontal region. In addition, gradual ramp up/down of stimulation intensity is considered very effective in blinding study participants (Rakel et al., 2010). Finally, equipment will be hidden in boxes to ensure that participant will be unable to see what the researcher is doing.

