### Interventions

An experienced physical therapist will manage the intervention protocols. During the intervention, participants will be comfortably seated in a chair, in silence. They will be encouraged to make no cognitive effort, such as mathematical calculations or complex reading. tDCS will be applied with a proper device (tDCS stimulator–TCT, China) connected with two silicon-sponge 5 × 7 (35 cm^2^) electrodes embedded in saline solution (0.9%). The anodic pole will be placed in the motor cortex region (M1) contralateral to the painful hip (or more painful in cases of bilateral symptoms) (locations C1 or C2, according to the 10/20 International EEG System). The cathodic pole will be placed over the contralateral supra-orbital region (locations Fp2 or Fp1, according to the 10/20 International EEG System). The 2 mA stimulation will last 20 min, ramped up and down for 30 s at the initial and final stages of stimulation. A clinical pulse generator (Endophasys, KLD Medical Products, Brazil) will be used to administer PES using 35 cm2 dischargeable electrodes located on the side of the most painful hip. The stimulation will start together with tDCS and will be held for 30 min. The intensity will be maintained at the sensory level, characterized as a comfortable intensity just under motor threshold, with pulse rate of 100 Hz and pulse duration of 200 μs.

Participants will be asked about their perception of the stimuli every 5 min during the intervention. For both tDCS and PES sham procedures, the devices will be ramped up for 30 s and then decrease until no electric current is delivered. To ensure blinding, participants will receive information that they may or may not feel the stimulation. Moreover, they will not be able to see the equipment. At the end of each intervention protocol, potential adverse effects and quality of blinding will be assessed by a self-report questionnaire.

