*Stage 1* (Sample characterization) will last ~40 min. The researcher will explain to the participant why and how to fill the socio-demographic and clinical questionnaires. The researcher will be available to clarify any doubts and help participant, if requested;*Stage 2* (Baseline assessment). EEG data will be collected during resting and Kinesthetic–MI conditions. Subsequently, in another room, the participant will receive instructions for the TMS cortical mapping. Following these electrophysiological assessments, a blood sample will be collected for BDNF and TNF serum level analysis. Finally, the pain intensity will be assessed. This stage may last up to 1 h and 30 min;*Stage 3* (Intervention). At this stage, the participant will be seated and the researcher will position the tDCS electrodes on the scalp according to the 10/20 EEG system. Electrodes will be fixed with an elastic band, comfortably adjusted. The PES electrodes will be positioned at the most painful hip. This stage will last around 40 min;*Stage 4* (Post-intervention assessment). In the last part of the study, the sequence of assessments will be slightly different from Stage 2. First, pain intensity will be measured. Then, a blood sample will be collected. Blood sample must be collected earlier in this stage to reduce circadian cycle effect on BDNF and TNF serum levels (Pan et al., 1985; Begliuomini et al., 2008). Finally, EEG data and TMS cortical mapping will be collected. The final stage is expected to last up to 1 h and 30 min.

Participants may take 5–10 min-breaks between all stages. During their time in the laboratory room, participants will have snacks and light beverage available at breaks. Participants will be reimbursed for transportation costs and receive a food voucher at the end of data collection.

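### The stated safeguard against tDCS skin redness ends with stimulation, before the primary pain rating, so it does not support the claim that participants cannot notice redness

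*Protocol article*

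**What the plan says.** In the protocol article, under Potential intervention biases, the authors cite a study of 30 min of tDCS in which supra-orbital erythema occurred, "ranging from mild to moderate, and may interfere with the study blinding". Their counter-measure is that "participants in this study will not be able to look at their faces during the stimulation procedure". They conclude: "Thus, they will not be able to recognize any erythema over their frontal region". The same paragraph adds that "equipment will be hidden in boxes to ensure that participant will be unable to see what the researcher is doing".

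Under Interventions, the return electrode is on the forehead: "The cathodic pole will be placed over the contralateral supra-orbital region". Active tDCS runs for 20 min. PES starts with it and runs for 30 min. Both sham procedures ramp up for 30 s and then fall to no current. Quality of blinding is assessed by a self-report questionnaire when the intervention protocol ends.

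Under Stepwise procedures, Stage 3 is the intervention and Stage 4 the post-intervention assessment. Stage 4 starts with pain intensity, followed by the blood sample. "Finally, EEG data and TMS cortical mapping will be collected". The section also states: "Participants may take 5–10 min-breaks between all stages".

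The section on study design calls the trial double blind and promises allocation secrecy until the analyses are finished. The Statistical analysis section keeps the analysts separate from data collection. The article does not say who takes the post-intervention measurements.

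**The concern.** The authors name a specific way in which the blind could fail and then treat it as closed. The measure they describe ends when stimulation ends, while every post-intervention outcome is collected later. The primary outcome is a self-rating, so what the participant believes about the treatment can act on it directly. Someone who uses the break and sees a reddened forehead may infer active tDCS just before rating pain.

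The safeguard is also worded for participants alone. A mark on the forehead can be seen by anyone facing the participant, and the post-intervention EEG uses Fp1 and Fp2, the two locations named for the tDCS cathode.

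At stake is the credibility of the comparisons between active and sham tDCS, including combined treatment against PES alone, which is one of the two single-technique comparisons in the hypothesis.

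**Working it through.** The plan states no figure on this point, so the check sets the passages side by side.

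**1. Does the conclusion follow from the safeguard?**

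| Element | Who | When |
|---|---|---|
| No view of own face | participant | during stimulation |
| Equipment in boxes, ramping, instructions | participant | intervention |
| Primary VAS | participant | after stimulation and any break |
| Blood, EEG, TMS | participant and measuring staff | after the VAS |
| Conclusion drawn | participant | no time limit |

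The conclusion has no time limit but its premise does. Nothing in the article covers the interval between the end of stimulation and the VAS.

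**2. How long is that interval?** Take Stage 4 to begin when PES ends, ignoring electrode removal, which is the same for all.
- From end of tDCS current to end of PES: 30 − 20 = 10 min.
- VAS without a break: about 10 min after the tDCS current ends.
- VAS with a break: 10 + 5 = 15 min to 10 + 10 = 20 min after it ends.

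The optional break therefore opens the opportunity to see the mark. It also lets the timing of the primary measurement differ by 0 to 10 min between participants.

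**3. What could a mark reveal?** Each arm has 16 participants per genotype and there are two genotypes, so 16 × 2 = 32 per arm.
- Active tDCS: arms 1 and 2, 2 × 32 = 64. Sham tDCS: arms 3 and 4, also 64.
- Combined (arm 1) against PES alone (arm 3): active against sham tDCS, 32 against 32. Exposed.
- Combined (arm 1) against tDCS alone (arm 2): both have active tDCS. Not exposed through this route.
- Combined (arm 1) against double sham (arm 4): exposed.

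**4. Would the blinding questionnaire catch it?** As written, it is given when the intervention protocol ends, which is before the break. It can record what participants believe at that moment, but not what they learn during the break. It is self-report, so it does not cover staff.

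**5. How sensitive is the test to a rating bias?** This is an illustration only. The bias *b* is an assumed average over all participants in the arm, in standard deviations of the quantity tested, and there is no true effect. A simple two-sided z test of two means with *n* per arm has false-positive rate

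1 − Φ(1.96 − b/√(2/n)) + Φ(−1.96 − b/√(2/n)).

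For n = 32, √(2/32) = 0.25:
- b = 0.1: 0.1/0.25 = 0.4, rate about 7%
- b = 0.2: 0.2/0.25 = 0.8, rate about 13%
- b = 0.3: 0.3/0.25 = 1.2, rate about 22%

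These rates show that a modest average bias would matter. They do not show that one will occur, and the z test is simpler than the planned repeated-measures ANOVA.

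**The case against.** The strongest reply is that the chain to participant unblinding is long. The participant must have redness that persists, take an optional break, see a reflection and read the mark as a sign of active current. The cited evidence comes from 30 min of tDCS against 20 min here, and about 10 min pass between the end of tDCS and the end of PES, so redness may have faded. Sham also begins with a ramp, and every participant wears EEG electrodes at Fp1 and Fp2 at baseline, so a mark need not be specific to active tDCS. The VAS is already first in Stage 4, blinding quality is assessed, and the analysts are kept apart from data collection.

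All of this bears on how likely and how large the problem is, and it stands to that extent. It does not repair the inference. The authors themselves judge the redness worth guarding against, and the guard they describe stops before the outcome it is meant to protect.

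A reader might go further and infer that the staff taking the measurements are unblinded. The article does not support that. It does not say who takes each measurement, and a fuller protocol may assign separate assessors. What can be said is only that the erythema safeguard as worded does not extend to them. Nor does the article say that the forehead is left uncovered after electrode removal. It is silent on this.

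**Conclusion.** The point holds in limited form. The conclusion that participants will notice no redness does not follow from a safeguard confined to stimulation, because a break is allowed before the self-reported primary VAS. The finding rests on the article's own account of the hazard, the safeguard and the schedule, and needs no outside figure.

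Its size is unknown. A reader might want to count how many of the 64 participants on active tDCS would be identified, but the article gives no rate, severity distribution or duration of redness, so any count would be invented. A reader might also take the mark to reveal the full allocation. It could indicate only active or sham tDCS, so the comparison of combined treatment with tDCS alone is not affected by this route. The one quantity that follows from the text is the avoidable spread of 0 to 10 min in VAS timing.

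This is a worthwhile, low-priority improvement to procedure and does not undermine the design.

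**What to change.** In Stepwise procedures, state that the post-intervention VAS is taken in the intervention chair before any break. The participant is already seated there and the VAS is taken seated in both positions, so this needs no new procedure. It also removes the 0 to 10 min spread in timing.

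In Potential intervention biases, extend the safeguard. Participants in all four arms wear an identical opaque forehead cover, with no mirror access, from removal of the tDCS electrodes until the VAS, the blinding questionnaire and the blood sample are done. Reword the conclusion so that it claims no more than this period.

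The cover also hides the mark from whoever takes the VAS and the blood sample. It must come off for the EEG, since Fp1 and Fp2 are recorded, so it does not protect the later EEG and TMS measurements.

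The cost is a headband worn briefly and a break that comes a few minutes later. Arms, stimulation settings and sample size do not change.

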### Measurement biases

*Gluteus maximus* muscle TMS mapping may be difficult because of its small and deep representation in the primary motor cortex. We aim to counteract this problem using active motor threshold and contraction during TMS assessment, a method successfully used by others (Lepley et al., 2013; Te et al., 2017). Neuronavigated TMS could further help with this measurement problem, but this resource is not available at the study laboratory. Nonetheless, the original study to validate TMS cortical mapping of the *gluteus maximus* muscle used a system similar to the one available for this study (Fisher et al., 2013).

### Potential confounders

A. Pain intensity

Emotional aspects such as anxiety and depression are commonly associated with chronic pain (Keefe et al., 2004). Anxiety and depressive symptoms are associated with increased sensitivity to experimental painful stimuli in individuals with SCD (Bakshi et al., 2017). In order to control for this confounding factor, symptoms of anxiety and depression will be evaluated pre-intervention using the HADS (Pais-Ribeiro et al., 2007).

B. Serum level BDNF and TNF

Circadian rhythm has influence on BDNF and TNF serum levels. A study with healthy subjects evaluated BDNF levels every 4 h and identified a continuous decrease throughout the day (Begliuomini et al., 2008). Similarly, an animal study demonstrated that levels of TNF also varies according to the circadian rhythm (Pan et al., 1985). To reduce the influence of circadian rhythm, data collection will start at the same time in the morning. Recent studies have shown that the presence of the Val66Met BDNF gene polymorphism may influence cortical neuroplastic changes and consequently the response to tDCS (Antal et al., 2010; Di Lazzaro et al., 2015). However, the population studied in this protocol will be mostly Afro-descendant of Yoruba origin, of which only 0.9% is heterozygous for the Met allele (Aken et al., 2016).

## Criteria of authorship

To be included as an author in the articles from this study, individuals should meet the following criteria of authorship (Petroianu, 2010):

Contribute substantially to the study conception and design; or to the acquisition, analysis, or interpretation of study data;Participate in the writing of this manuscript or critically examine its intellectual content.
